### **3.8     *End of study***

When the last included patient completes 12-month follow up, the study is ended.

The study cannot be early terminated based on the effectiveness results.

The patient can withdraw from the study at any time for any reason.

## **4 Statistics**

### **4.1 Sample size**

#### **4.1.1 Assumptions**

At 12 months after implantation, the patients in QuickOpt™ optimization group shall have the LVESV improvement at least the same as that of the echocardiographic optimization group at the assumed lower limit of -10%.

#### **4.1.2 Calculation of sample size**

It is assumed that the significant difference is 0.05 (one-sided), test power is 80%, overall standard derivation is 0.35, and the difference between two group mean is 0.1, the total sample size is 306, with 153 in each group; in consideration of 20% of drop-out rate as a result of death, heart transplantation, loss to follow-up during this study, the total sample size is 382, with 191 in each group. The final total sample size is 400, with 200 in each group.

According to the implantation proportion of CRT-P and CRT-D, for the total 400 patients, it is estimated to include 260 patients for CRT and 140 for CRT-D. The randomized table is generated in a 1:1 ratio for respective sample size.

### **4.2 Statistical method**

*t*-test will be performed for primary endpoint, LVESV. In case of significantly abnormal distribution and heterogeneity of variance, one of the following non-parametric tests will be performed based on the distribution of final data: Wilcoxon rank sum test, rank test, rank sum test or Kolmogorov-smirnov test.

For secondary endpoint, Cochran-Mantel-Haenszel test will be performed for the comparison of improvement of NYHA class and SAS assessment between these two methods. If the chi-square test indicates homogeneous distribution, Fisher's exact test will be performed. *t*-test is performed for the difference in the improvement of 6-MHWD between these two methods. In case of significantly abnormal distribution and heterogeneity of variance, one of the following non-parametric tests will be performed based on the distribution of final data: Wilcoxon rank sum test, rank test, rank sum test or Kolmogorov-smirnov test.

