## **2.4 Study design**

This is a prospective, randomized, double-blind, multicenter (Mainland China), parallel control, non-inferiority, and postmarketing study. The patients who were implanted with CRT-P or CRT-D are randomized to QuickOpt™ optimization group or echocardiographic optimization group in a

1:1 ratio within two weeks after implantation, and followed-up at 3 ( $\pm 2$  weeks), 6 ( $\pm 2$  weeks), and 12 ( $\pm 2$  weeks) months after implantation. In addition to 12 months after implantation, the patients will undergo interval optimization with corresponding method at enrollment, 3 and 6 months, and the optimal AV interval obtained by the optimization are programmed to the patients' CRT-P/D; it is necessary to determine and collect the clinical data at each follow-up.

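### Section 4.2 does not tie the primary LVESV test to the -10% non-inferiority limit, and it leaves the fallback test to be picked from the final data

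*Protocol*

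**What the plan says.** - **Design.** Section 2.4 calls the trial a "parallel control, non-inferiority, and postmarketing study". Section 2.1.1 asks whether QuickOpt can serve as an alternative to echocardiographic optimization.
- **Limit.** Section 4.1.1 requires the QuickOpt group's LVESV improvement to be "at least the same as that of the echocardiographic optimization group at the assumed lower limit of -10" per cent. This is the only place where the limit is stated as such.
- **Sizing.** Section 4.1.2 uses one-sided 0.05, 80% power, SD 0.35 and a difference of 0.1. It arrives at 153 per group, 382 in total after 20% drop-out, and finally 400 (200 per group).
- **Primary analysis.** Section 4.2 names a t-test with a fallback, in the words "will be performed for primary endpoint, LVESV. In case of significantly abnormal distribution and heterogeneity of variance, one of the following non-parametric tests". The candidates are "Wilcoxon rank sum test, rank test, rank sum test or Kolmogorov-smirnov test", and the choice among them depends on how the final data turn out to be distributed.
- **Same wording elsewhere.** Section 4.2 gives 6-MHWD, a secondary endpoint with no margin, the same t-test and the same fallback list.

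**The concern.** A non-inferiority conclusion needs the estimated difference, with its uncertainty, to be set against the margin. Section 4.2 never mentions the margin, a shifted null hypothesis, a confidence interval or the one-sided level. The same t-test wording covers 6-MHWD, where it plainly means a comparison for difference, so an analyst could apply a test of zero difference to LVESV as well.

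The fallback adds a second problem. No rule selects among the listed tests, so the choice stays open until the results can be seen. The options also do not answer the same question. Kolmogorov-Smirnov tests for any difference between two distributions and gives no location estimate to compare with -10%. A rank sum test could serve, but only with a shift by the margin or an accompanying Hodges-Lehmann interval, and neither is specified.

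What is at stake is the trial's central claim. If failure to find a difference stood in for non-inferiority, the 5% error rate for which the trial was sized would no longer be controlled.

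**Working it through.** **Inputs** (Section 4.1.2 unless noted): margin 0.10 (Section 4.1.1: -10%), SD 0.35, one-sided alpha 0.05, power 80%, true difference taken as 0, 1:1 allocation.

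**Step 1: reproduce the plan's sample size.** With the normal approximation,

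n per group = 2 × (z₀.₉₅ + z₀.₈₀)² × SD² / margin² = 2 × (1.645 + 0.842)² × 0.35² / 0.10² ≈ 151.5, so 152.

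The exact non-central t calculation gives 153 per group (power 80.2%), which is the plan's figure. One-sided 0.025 gives 193 (normal) or 194 (t) and does not match. The drop-out step is 306 / 0.8 = 382.5, against the stated 382. The sizing is therefore a sound one-sided 0.05 calculation against a 0.10 margin.

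**Step 2: error rate if non-significance were read as non-inferiority.** Suppose QuickOpt is truly worse by the full 0.10. The standard error is 0.35 × √(2/n), and the non-centrality is 0.10 / SE.

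- n = 153: SE = 0.0400, non-centrality 2.50, df 304.
- n = 160 (400 × 0.8 / 2): SE = 0.0391, non-centrality 2.56, df 318.
- n = 200: SE = 0.0350, non-centrality 2.86, df 398.

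The probability that a t-test of zero difference is not significant is the non-central t probability below the critical value:

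| Evaluable per arm | Two-sided 5% | One-sided 5% | Intended |
|---|---|---|---|
| 153 | 29.8% | 19.8% | 5% |
| 160 | 27.8% | 18.3% | 5% |
| 200 | 18.7% | 11.4% | 5% |

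Under the same reading, simulation with normal data (4,000 runs, 153 per arm, two-sided 5%) gives about 32% for the Wilcoxon test and about 44% for Kolmogorov-Smirnov with asymptotic p-values. The error rate therefore also depends on which test is picked.

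**Step 3: the same data tested against the margin.** A t-test shifted by 0.10, or equivalently the lower limit of the two-sided 90% interval compared with -0.10, holds the error at 5% (5.3% in the simulation). Its power at a true difference of 0 is 80.2% at 153 per arm, 81.7% at 160 and 88.6% at 200. No extra patients are needed.

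**The case against.** The strongest reply is that Section 4.2 says only that a t-test will be used. A t-test shifted by the margin is still a t-test, and it is the one that reproduces 153 per group. Section 4.2 belongs to the same chapter as the -10% limit and the one-sided level, and a separate SAP could carry the confidence-interval rule. This stands in part. A reader might infer that the protocol prescribes a test of no difference and so cannot support non-inferiority. The text does not go that far: it states no null hypothesis at all.

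The rates in the table are also those of a decision rule that the protocol never adopts. They show what the gap would allow and are not the error rate of the plan as such.

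Four further inferences should be resisted:

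- **That unequal variance alone triggers the fallback.** The text joins abnormal distribution and unequal variance with the word *and*.
- **That Kolmogorov-Smirnov's tendency to reject when means are equal but spreads differ shows false non-inferiority.** It does not. If non-significance counted as success, such a rejection would count against QuickOpt. Any figure for it would also need SDs that the protocol does not give.
- **That the Wilcoxon test misbehaves here under unequal variances.** With equal means and assumed SDs of 0.28 and 0.42 at 160 per arm, its simulated rejection rate is 5.2%, so no harm is shown.
- **That the limit means 10 percentage points.** Section 4.1.1 does not define the scale, and Sections 2.2.1 and 4.2 name LVESV without a change measure.

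The reply does not remove the central point. Section 4.2 is not merely silent: it fixes a menu of methods, chosen on the final data, and at least one of them cannot be compared with a margin. An SAP that specified a margin-based analysis would have to overrule that menu.

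**Conclusion.** The point holds in a limited form. The design and the sample size are coherent with each other, but Section 4.2 does not connect the primary test to the -10% limit and one-sided 0.05. It also leaves the fallback to a post-data choice that includes a test with no estimate to set against a margin. From Section 4.2 alone, nobody can tell what result would establish non-inferiority.

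The size is conditional. If non-significance were taken as non-inferiority, the false-conclusion rate at a true deficit of 0.10 would be about 30% or 20% (two-sided or one-sided 5%) at 153 per arm, and 19% or 11% at 200 per arm, against 5% intended. These figures assume a common SD of 0.35 and the t-test. The sample size itself is not in question.

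**What to change.** Rewrite the primary-endpoint paragraph of Section 4.2 as follows:

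1. **Decision rule.** Non-inferiority is concluded if the lower one-sided 95% confidence limit (the lower limit of the two-sided 90% interval) for the QuickOpt minus echocardiography difference in LVESV improvement lies above the -10% limit.
2. **Scale.** Define improvement and its sign so that they match the 0.10 margin and 0.35 SD of Section 4.1.2. These appear to be proportional change from baseline, but the sponsor must confirm this. Use the same definition in Sections 2.2.1 and 4.1.1.
3. **One primary method**, valid under unequal variances, for example a Welch interval.
4. **One prespecified fallback or sensitivity analysis** that gives an interval on the same scale, for example a Hodges-Lehmann shift with its confidence interval, judged against the same limit.
5. **Delete** the data-driven menu and the Kolmogorov-Smirnov option.

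The cost is protocol or SAP wording before database lock. No patients or data are added, and power stays at 80.2% with 153 evaluable per arm under the plan's own assumptions.

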### **2.2 Study endpoints**

#### **2.2.1 Primary endpoint**

Cardiac remodeling indicator at 12 months after implantation: LVESV

To minimize the disadvantages of poor reproducibility and large accidental error for echocardiographic measurement, the enrolled patients in each site will be performed with echocardiography by the Echocardiographic Core Laboratory for uniform measurement in this study.

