#### 3.2.1 Randomization

The CRT-P patients are randomized to QuickOpt™ optimization group or echocardiographic optimization group in a 1:1 ratio as per the randomized table with sample size of 260.

The CRT-D patients are randomized to QuickOpt™ optimization group or echocardiographic optimization group in a 1:1 ratio as per the randomized table with sample size of 140.

- QuickOpt™ optimization group: The patients' pacemaker is programmed according to the results of QuickOpt™ optimization (optimized sensing AV interval, optimized pacing AV interval and optimized VV interval). Time of follow-up requiring optimization: baseline (within two weeks after implantation), 3 ( $\pm 2$  weeks) months and 6 ( $\pm 2$  weeks) months; in addition, the investigator should determine whether to optimize interval at unscheduled follow-up.
- Echocardiographic optimization group: The patients' pacemaker is programmed according to the results of echocardiographic optimization (optimized sensing AV interval, optimized pacing AV interval and optimized VV interval). The same as QuickOpt™ optimization group for others. No specific requirement for specific method of echocardiographic optimization is set in this study and the method is determined by each site. The optimization sequence is from AV/PV interval to VV interval based on optimized PV interval. Please refer to the Appendix.

In this study, the patients will not be informed of the randomization to QuickOpt™ or echocardiographic optimization group.

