##### ① Clinical Data

- Basic information of the patients
- 12-lead ECG (non-pacing & pacing)
- Chest X-ray (**PA+LAO 45°**)
- Information on pacing system implantation
- Pacemaker follow-up: the diagnostic criteria for atrial and ventricular arrhythmia (at

discretion of the investigator) will be programmed and AMS opened

- For CRT-P, it is necessary to open the EGM Storage in trigger chamber for rapid ventricular rate

Printing: diagnostic data, programmer test results, final programmed parameters

For QuickOpt™ group, it is necessary to print the QuickOpt™ test results

Storage: CRT-P stores the PDF of print contents.

CRT-D stores Session Record

- Zeroing out: diagnostic data zeroed out after printing and storage
- ② Optimization: optimize AV interval according to randomized group and program the optimization results to the pacemaker. If it fails to program based on the optimization results, it is necessary to complete the “protocol deviation form”.

Note: If the result of echocardiographic optimization is RV pacing first, to obtain appropriate left AV interval, the result of subtracting the optimized VV interval value from the optimized AV/PV interval is used as the AV/PV interval value for programming. Similarly, for current QuickOpt™, the optimization algorithm is to optimize AV interval and VV interval. Therefore, after QuickOpt™ optimization, if the result is RV pacing first, to obtain appropriate left AV interval, the result of subtracting the optimized VV interval value from the optimized AV/PV interval should be used as the AV/PV interval value for programming.

- Drug therapy

(2) Items in the charge of the blinded investigator:

NYHA class

SAS (refer to the appendix)

6-MHWD (refer to the appendix)

(3) Items in the charge of the echocardiography technician :

- Echocardiogram (stored in the disk in DICOM form to deliver to the core echocardiography laboratory for measurement)

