### **3.4 12-month follow up after implantation**

- (1) Time-window:  $\pm 2$  weeks
- (2) Clinical data: echocardiogram data, SAS and 6-MWHD , other data is same as 3 month follow up
- (3) Optimization: not required

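### The primary t-test adjusts for neither baseline LVESV nor device stratum; it is valid and powered as planned, but adjustment would add precision at no cost in patients, by an amount the documents do not determine.

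*Protocol*

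**What the plan says.** - **Primary analysis.** Section 4.2 says a t-test "will be performed for primary endpoint, LVESV". If the data are clearly non-normal with unequal variances, one of several rank tests or a Kolmogorov-Smirnov test replaces it. No covariate or stratum is named for any of these.
- **Endpoint.** Section 2.2.1 gives "Cardiac remodeling indicator at 12 months after implantation: LVESV". Section 4.1.1 instead frames the hypothesis as LVESV improvement, with a lower limit of -10%.
- **Baseline measurement.** Section 3.2.2 lists among the baseline items "Echocardiogram (stored in the disk in DICOM form to deliver to the core echocardiography laboratory for measurement". Section 3.4 collects "echocardiogram data, SAS and 6-MWHD , other data is same as 3 month follow up" at 12 months. Table 1 likewise shows a core-laboratory echocardiogram at these two visits.
- **Randomisation.** In section 3.2.1, CRT-P patients are allocated "as per the randomized table with sample size of 260" and CRT-D patients "as per the randomized table with sample size of 140". Section 4.1.2 repeats this: "The randomized table is generated in a 1:1 ratio for respective sample size". Device type is therefore a stratification factor.

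**The concern.** Section 2.4 calls the trial a non-inferiority study. The result will turn on how far the lower confidence limit lies from -10%, and so on the standard error. A patient's LVESV at 12 months usually depends on LVESV at entry. A two-sample test leaves any such dependence that the outcome has not already absorbed in the error term. It also leaves in the difference any chance imbalance in starting heart size. Separately, a test that ignores the randomisation strata uses a standard error slightly too large for the design. Both variables are collected anyway, so the question is how much precision the named test gives up.

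The protocol itself fixes the primary test, so this is not simply detail left to an analysis plan.

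**Working it through.** **Inputs from section 4.1.2:** one-sided alpha 0.05, power 80%, SD 0.35, difference 0.1, dropout 20%, 200 per arm. **From section 3.2.1:** 260 CRT-P and 140 CRT-D, so the CRT-D share is 140/400 = 0.35. **Not in the documents:** any correlation with baseline and any CRT-P versus CRT-D difference. Those below are assumptions.

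**1. The plan's own figure.** Taking 0.1 as the margin with a true difference of zero, n per arm = 2 × [0.35 × (1.645 + 0.842)/0.1]² = 151.5, so 152 (304 in total). The exact t calculation gives 153 per arm, or 306, as stated. Power by normal approximation is Φ(0.1/(SD × √(2/n)) − 1.645). With SD 0.35 it is 80.3% at n = 153 and 81.9% at n = 160 (200 less 20%). The plan's size matches an unadjusted test, with no allowance for adjustment.

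**2. Outcome is a simple change score with SD 0.35.** With equal variances at the two visits and baseline to 12-month correlation r, adjusting for baseline multiplies the variance by (1 + r)/2.

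| r (assumed) | Variance ratio | Adjusted SD | n per arm for 80% | Power, 153 per arm | Power, 160 per arm |
|---|---|---|---|---|---|
| 0.5 | 0.75 | 0.303 | 114 | 89.3% | 90.4% |
| 0.6 | 0.80 | 0.313 | 122 | 87.5% | 88.7% |
| 0.7 | 0.85 | 0.323 | 129 | 85.7% | 87.0% |
| 0.8 | 0.90 | 0.332 | 137 | 83.9% | 85.3% |

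**3. Outcome is relative change.** The unitless 0.35 and the -10% limit suggest this. The variance ratio is then 1 − c², where c is the correlation of baseline with relative change. Two assumed models show the spread.

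- *No gain.* Let 12-month LVESV = baseline × G, with G independent of baseline, mean 0.8 and SD 0.35. Then c = 0 by construction. With baseline coefficient of variation k, the baseline to 12-month correlation is 0.8k/√(0.1225 + 0.7625k²). This is 0.55 at k = 0.3 and 0.71 at k = 0.5. A substantial correlation between visits is thus compatible with no gain at all.
- *Moderate gain.* Let both volumes be log-normal with log-SD 0.35 (log-variance 0.1225) and log-scale correlation r. Then c = (exp(0.1225(r − 1)) − 1)/√[(exp(0.1225) − 1)(exp(0.245(1 − r)) − 1)]. This is −0.46 at r = 0.5 and −0.30 at r = 0.8, a variance cut of 21% and 9%. If 0.35 is the SD of the analysed outcome, power at 153 per arm is about 88% and 83.5%.

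**4. Outcome is raw 12-month LVESV.** The variance ratio is 1 − r². The cut is 25% at r = 0.5 and 64% at r = 0.8. The planning SD of 0.35 is not on this scale.

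**5. Device type alone.** For a difference D between device types in mean outcome, the share of variance explained is 0.35 × 0.65 × D²/0.35².

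| D (assumed) | Share explained | n per arm for 80% | Power, 153 per arm | Actual one-sided alpha if ignored |
|---|---|---|---|---|
| 0.05 | 0.5% | 151 | 80.5% | 0.0496 |
| 0.10 | 1.9% | 149 | 81.0% | 0.0484 |
| 0.15 | 4.2% | 146 | 81.8% | 0.0464 |
| 0.20 | 7.4% | 141 | 83.0% | 0.0437 |

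The last column is 1 − Φ(1.645/√(1 − share)). Ignoring the strata makes the test slightly conservative, never liberal.

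**6. Timing of the covariate.** Section 3.2.2 lists the first optimisation among the clinical investigator's items and the echocardiogram among the technician's, without saying which comes first. A baseline volume recorded after optimisation could already carry some treatment effect.

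**The case against.** The strongest reply is that nothing here is wrong. Under 1:1 randomisation the t-test is unbiased, device type is balanced by design, and the stated sample size follows from the stated test. All of that stands.

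Three stronger readings are tempting, and the documents do not support them.

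- *The analysis ignores baseline altogether.* A reader might infer this from sections 2.2.1 and 4.2, which name LVESV alone. But section 4.1.1 works on improvement, and the planning SD and difference fit a relative change. On that reading baseline already enters the outcome in part.
- *Adjustment would bring power to 85% to 90%.* That range (at 160 per arm) needs a simple change score, equal variances and an assumed correlation. The multiplicative example shows that the gain can be zero.
- *Ignoring the strata is a serious fault.* The effect is small and in the conservative direction.

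It can also be said that covariates belong in the analysis plan, which is not at hand. That has some weight. However, section 4.2 does name the primary test and its fallbacks, all unadjusted, so a plan that made an adjusted model primary would depart from it. Finally, the outcome scale is a more basic question than the choice of covariates. This is true, and the fix has to settle it.

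**Conclusion.** The point holds as a free improvement, not as an error or a validity problem. The named test achieves its 80% power at 153 per arm. Adjusting for baseline LVESV would do no material harm and could help. The size of the help is unknown: near zero if relative change is unrelated to baseline, about 84% to 89% power at 153 per arm (85% to 90% at 160) for a simple change score with correlation 0.8 to 0.5, and more for raw 12-month LVESV. Nearly all of any gain comes from baseline LVESV. Device type adds about 0 to 3 power points for assumed differences up to 0.20, and its main merit is that the standard error then matches the stratified randomisation. The facts about the test, the baseline echocardiogram and the two tables are certain; every gain figure rests on assumptions the documents neither give nor exclude.

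**What to change.** In section 4.2:

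1. State the outcome on the same scale as the -10% limit. This is either relative LVESV improvement, or log LVESV with the limit converted and the conversion shown.
2. Pre-specify as primary a linear model of that outcome with treatment, baseline LVESV and device type (CRT-P or CRT-D).
3. Compare the one-sided 95% confidence limit for the adjusted difference, QuickOpt minus echocardiographic optimisation, with the limit.
4. Specify that the covariate is the core-laboratory LVESV from an echocardiogram recorded before the first optimisation.
5. Analyse 6-MHWD in the same way with its own baseline, which Table 1 already collects.
6. Keep the unadjusted t-test as a supportive analysis.

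The cost is protocol and analysis-plan wording, plus an instruction to sites on the order of the baseline echocardiogram and the first optimisation. No extra patients, visits or measurements are needed. The change should be made before any unblinded data are seen, so that the model cannot appear to have been chosen by its result.

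### Protocol 4.2 triggers Fisher's exact test for NYHA class and SAS on a chi-square finding of homogeneity, which is the wrong condition; the rule is conservative and its power cost depends on how improvement is coded

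*Protocol*

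**What the plan says.** Protocol 2.2.2 lists NYHA class, SAS and the 6-minute walk at 12 months as secondary endpoints. For the first two, Protocol 4.2 states: "Cochran-Mantel-Haenszel test will be performed for the comparison of improvement of NYHA class and SAS assessment between these two methods". The next sentence sets the rule at issue: "If the chi-square test indicates homogeneous distribution, Fisher's exact test will be performed".

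Section 4.2 gives no level for the chi-square step, no criterion based on expected counts, no strata or scores for the CMH test, and no coding of improvement (yes/no or several levels). Device type is a natural stratum because Protocol 3.2.1 and 4.1.2 give CRT-P (260) and CRT-D (140) separate 1:1 randomisation tables, but 4.2 does not name it.

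**The concern.** Fisher's exact test is used when a table is too sparse for the large-sample chi-square approximation. Whether the chi-square result is significant has no bearing on that.

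- If homogeneous means no difference between the arms, the result of one test of the hypothesis decides which test of the same hypothesis is reported.
- If it means homogeneity across strata, the rule drops CMH in the situation that suits it best.

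Neither reading gives a valid trigger. This is more than a detail left open for an analysis plan, because the protocol fixes a rule and fixes it badly. At stake is the sensitivity of the NYHA and SAS comparisons. When the chi-square test is non-significant, Fisher's test on the same table almost always is too, so a shift that CMH would have detected can go undetected.

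**Working it through.** **The plan's own figure.** The protocol gives no figure for the NYHA or SAS tests; its only calculation is for LVESV. The inputs in 4.1.2 are: "It is assumed that the significant difference is 0.05 (one-sided), test power is 80" per cent, "overall standard derivation is 0.35", and "the difference between two group mean is 0.1". The normal approximation gives 2 × (1.645 + 0.842)² × 0.35² / 0.1² ≈ 151.5, so 152 per arm. The noncentral t gives 79.96% power at 152 and 80.2% at 153. This reproduces "the total sample size is 306, with 153 in each group". With 20% drop-out, 306 / 0.8 = 382.5, against the stated 382. None of this depends on the rule in 4.2.

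**Inputs for the check.**
- Completers: 400 × 0.8 = 320, or 160 per arm. By device and arm: CRT-P 260 × 0.8 / 2 = 104; CRT-D 140 × 0.8 / 2 = 56.
- Assumed, not in the protocol: two-sided 5% for every test; Fisher's replaces CMH after a switch; CMH uses row mean scores stratified by device; proportional-odds shifts of 1.5, 1.75 and 2.0; the category probabilities in the table.

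**The rule as simulated.** Compute the Pearson chi-square on the pooled table. If p ≥ 0.05, use Fisher's test (Freeman-Halton for more than two levels); otherwise use CMH. Then

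P(rule significant) = P(chi-square p < 0.05 and CMH p < 0.05) + P(chi-square p ≥ 0.05 and Fisher p < 0.05).

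**Step 1: the second term is negligible.** With Fisher's test actually run, it was significant after a switch in at most 0.4% of all trials (3,000 trials per scenario for two and three levels, 2,000 in one scenario with differing device strata). A 250-trial run with four levels found none. The 100,000-trial runs below therefore set this term to zero.

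**Step 2: no true difference.** A 5% chi-square test is non-significant in 1 − 0.05 = 95% of trials (simulated 95.0 to 95.3%). Rejection rates, CMH alone against the rule: yes/no 4.8% and 4.7%; three levels 5.0% and 2.5%; four levels 5.1% and 1.9%. The rule does not inflate type I error.

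**Step 3: true difference.** Losses are taken from unrounded values.

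| Assumed levels | Odds ratio | Switch to Fisher | CMH alone | Rule | Loss (points) |
|---|---|---|---|---|---|
| Yes/no, 60/40% | 1.5 | 59.2% | 40.9% | 40.8% | 0.1 |
| | 1.75 | 34.3% | 65.7% | 65.7% | 0.0 |
| | 2.0 | 17.9% | 82.0% | 81.9% | under 0.1 |
| Three, 55/35/10% | 1.5 | 65.7% | 42.2% | 30.9% | 11.3 |
| | 1.75 | 40.9% | 67.8% | 56.3% | 11.5 |
| | 2.0 | 22.3% | 84.2% | 75.9% | 8.3 |
| Four, 25/45/25/5% | 1.5 | 65.9% | 48.8% | 30.9% | 17.8 |
| | 1.75 | 39.9% | 75.4% | 58.1% | 17.3 |
| | 2.0 | 19.8% | 90.7% | 79.2% | 11.5 |
| Four, 25% each | 1.5 | 63.7% | 52.2% | 33.5% | 18.6 |
| | 1.75 | 36.4% | 79.1% | 62.0% | 17.0 |
| | 2.0 | 16.9% | 92.7% | 82.5% | 10.2 |

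With a yes/no outcome the pooled chi-square and CMH are nearly the same test, so requiring both costs almost nothing. If CRT-P and CRT-D differ strongly in prognosis, the yes/no loss at an odds ratio of 1.75 rises to about 1 to 2 points.

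**Cross-check.** A separate simulation used 160 per arm, the 25/45/25/5% distribution, 3,000 trials per scenario and Fisher p-values by Monte Carlo. It gave 48% for CMH and 31% for the rule at an odds ratio of 1.5, in line with the table.

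**The case against.** Several points on the other side stand.

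- **Replacement is inferred.** The protocol says that Fisher's test will be done, not that it supersedes CMH. Substitution is the likelier reading, because the parallel clauses in 4.2 on non-parametric tests work that way. If Fisher's is only an addition, CMH still stands and no power is lost.
- **The 95% measures no harm in itself.** It is one minus an assumed 5% level, and a non-significant answer is correct when there is no difference.
- **The loss depends on coding that the protocol does not fix.** The category probabilities and odds ratios also come from outside it.

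A reader might infer two stronger claims that the protocol does not support. The first is that the rule discards an ordinal test stratified by device. Section 4.2 names neither scores nor strata; both were chosen for the check. The second is that the rule tilts the trial towards declaring the two methods interchangeable. The -10% limit in 4.1.1 and the sample size concern LVESV, the sole primary endpoint. Section 2.1.1 lists NYHA class and SAS under the primary objectives, but only as changes to be assessed, with no margin or success rule. Nothing says that a non-significant result on either will be read as equivalence, and that misreading would be just as possible with CMH alone.

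None of this rescues the condition itself. Even if the sentence is a slip for small expected counts, an analyst who followed it would do something else.

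**Conclusion.** The point holds as a wrong trigger on two secondary endpoints. That conclusion needs no simulation: neither reading of homogeneous justifies moving to Fisher's test, and nothing else in the protocol corrects the sentence.

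The size is conditional. If Fisher's replaces CMH and the chi-square step tests the arms at 5%, the rule in effect demands significance on both tests. Its cost then runs from almost nothing (improved yes/no) to about 8 to 19 points of power (three or four ordered levels), under the assumptions listed. If homogeneity across strata was meant, the condition is still wrong but these power figures do not apply. The rule errs towards caution, and the LVESV analysis is not touched.

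**What to change.** Delete the sentence on Fisher's test in 4.2. Keep CMH as the single planned test for NYHA class and SAS, stratified by device type because CRT-P and CRT-D are randomised from separate tables. Allow an exact version only when expected cell counts are small, for example below 5, whatever the chi-square result.

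If improvement is analysed on ordered levels, row mean scores are a sensible accompanying choice; their absence from 4.2 is not part of the error.

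The cost is one sentence removed and a short clause added. Enrolment, data collection, sample size and the primary analysis do not change.
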